## 8.0 Sample Size

A total of 600 couples will be enrolled from the three study sites. Enrollment will be competitive. All couples will participate in the longitudinal cohort study. A subset of up to 60 couples per site will be invited to participate in qualitative in-depth interviews and focus group discussions.

## 9.0 PrEP Medication

Tenofovir disoproxil fumarate (or TDF, 9-[(R)-2-[[bis[[[isopropoxycarbonyl]oxy]methoxy]phosphinyl] methoxy]propyl]adenine fumarate) and emtricitabine (or FTC, 5-fluoro-1-(2R,5S)-[2-(hydroxymethyl)-1,3-oxatholan-5-yl]cytosine) are reverse transcriptase inhibitors that have been approved for the treatment of HIV-1 infection in humans in Nigeria. A fixed-dose, oral co-formulation of FTC with TDF, which carried the trade-name Truvada®, will be used in this study. PrEP will be prescribed for once-daily use. Study medication will be donated by Gilead Sciences.

## 10.0 Recruitment

Each site will develop local recruitment and screening methods that operationalize protocol-specified requirements for eligibility determination in a manner that is tailored to and most efficient for the local study setting and target study population. The design of local recruitment and screening methods would be informed by the outcome of the PrEP formative study.

Recruitment strategies will include partnering with existing HIV counseling and testing (HCT) centers and CSOs working with families and couples, public promotion of couples HCT by well-known figures and community organizations such as churches and mosques, and community mobilization around couples HCT promotion (during Valentine's Day and World AIDs day).

Recruitment materials will educate couples about the probability of being HIV-1 serodiscordant based on available data, and risks of unknown HIV-1 serodiscordancy in terms of transmission to the HIV-1 uninfected partner, and will emphasize the benefits of couples HCT with specialized counseling services. Couples may be recruited for possible inclusion in the study through referrals from HCT centers and other community-based organizations, direct outreach, or other activities conducted at the study sites.

Regardless of the recruitment source, each partner in each couple will provide independent informed consent for screening. The screening process will proceed in a step-wise manner for both partners until either all screening procedures are completed or one or both of the partners is determined to be ineligible.

Although all required screening procedures may be completed in as few as two visits for each partner, additional visits may be conducted as needed (for example, if one or both partners want more time to consider whether to enroll in the study). At least one screening visit and the enrollment visit must be attended by both partners of a couple together, and at least one couple counseling session must take place during the screening process. There is no time limit on the screening process.

For those couples found to be eligible for the study, informed consent for study participation and enrollment in the study may proceed on the same day when eligibility is

---

57 There is an ongoing PrEP formative study that would enable stakeholders engage with the design of appropriate communication and recruitment strategies for male and female HIV serodiscordant couples for this study.

determined. Each partner will be asked to provide independent informed consent for study participation.

## 11.0 Study Procedures

It adopts the Partner's PrEP study approach as discussed at the WHO Demo Meeting in July 2012. The anticipated total study duration is approximately 24 months, with accrual requiring approximately 6 months and follow-up continuing for approximately 18 months after the end of the accrual period. Potential study participants will be screened for eligibility and eligible participants will be enrolled in the study within 30 days of screening. Visits will take place at screening and enrollment, a visit 1 month after enrollment, and then quarterly thereafter, for up to 18 months.

### 11.1 Community education and mobilization

In line with outcomes of the PrEP formative research, and lessons learnt from past HIV prevention trial efforts, community engagement is key and critical. This study will build on the lessons learnt from the NICCAV project, a HIV vaccine demonstration project in Nigeria. It will adopt its community engagement structure for this study. The project will work with a not-for-profit organization as an operations partner for the community mobilization program for the project. The organization will build the capacity of other identified community based partner organizations working in the various communities hosting the trial sites to conduct public education and support for the project. The capacity building effort will be such that seeks to have the partners integrate public education on PrEP and biomedical HIV prevention as an integral component of the organizational activities. This would ensure sustained public education effort long after the conclusion of the demonstration project.

#### 11.1.1 Project Community Advisory Board (CAB)

Lessons learnt from the NICCAV project and other projects of such magnitude in Nigeria will be used to cultivate community support and assist in the establishment of an active Community Advisory Board (CAB) with representative from various community sectors. Consultations will be held with key stakeholders, and communities at the site of the project will continually be educated about HIV, AIDS, biomedical HIV prevention, PrEP and the role of research in HIV prevention. Once established, the CAB will play an advisory role to the project. The capacity of the members of the CAB will be built by the reference organization engaged with the NICCAV project in Nigeria so that they are involved in discussing the research from an informed perspective. A structured capacity building process that will enable members give constructive feedback on research protocols, monitor the project as community representatives, and disseminate information about the research to their respective constituencies will be developed. Lessons learnt and best practices from other studies will be shared with communities at the three study sites to ensure full community participation and retention.

---

 On the 21st and 22nd of July, 2012, WHO hosted a meeting of the PrEP working group to develop consensus on a framework for country level protocol development for Pre-Exposure Prophylaxis (PrEP) demonstration projects. The working group reached consensus on elements to be included in country demonstration project protocols. The meeting recommended that demonstration projects should follow the Partners PrEP demonstration project model

### 11.1.2 Community education

The Project Community Liaison Officer will work with the CAB and local community groups to disseminate culturally and linguistically appropriate information pertinent to the study within the communities at the study sites. Educational materials will be developed through a community consultative process to ensure culture representation and language appropriateness. The community engagement efforts would address community norms that would otherwise impede patient use of and adherence to antiretroviral-based HIV-1 prevention services.

### 11.1.3 Interaction with the media

The communication working group, hosted by the Corporate Communication Unit of NACA, would work with the media to promote public awareness and education about the PrEP study and public support for PrEP use by sero-discordant couples. Public communication mechanism shall be designed based on specific community needs. The electronic and print media shall be engaged extensively for this project. In addition, the local town criers in target study communities would be engaged to facilitate local community announcement of the study.

## 11.2 Study site preparation

As part of the study intervention, a QI approach will be used to assist the service delivery outlets expand their current services to include PrEP and TasP provision. An experienced QI advisor will work with the staff at the service delivery outlets to conduct a gap analysis of existing service provision prior to the enrollment of study participants at these sites. External and internal ideas will be carefully vetted to improve the quality of service delivery in the areas of family planning counseling and contraception provision, STI and HIV counseling and treatment, and general clinic processes (e.g. clinic flow, documentation, follow-up). The QI advisor will undertake ongoing monitoring of the quality of each of these services. Once the initial QI process has been completed at the participating service delivery outlets, a site initiation assessment will be undertaken to ensure procedures are in place for the study including procedures for dispensing PrEP and TasP. Once each service outlet meets the requirements for site initiation, study participants will be enrolled and the same QI approach will be used to integrate reliable PrEP and TasP provision and monitoring into the service delivery programs.

Specific steps used in the QI approach to be implemented in the hospitals that hosts the service delivery outlets include:

- Acknowledgement that service delivery outlet (out-patient clinic or HIV service delivery clinic) need to be strengthened and improved
- Clear commitment by facility-based staff to specific time-limited aims to ensure improvements to the quality of services to be provided
- Completion of a facility audit to identify nature of challenges and bottlenecks in system that impede service delivery
- Establishment of a clinic-based multi-disciplinary “improvement team”
- Goals and timelines for rapid improvement of outcomes set

- Mapping of relevant clinic-based processes for service provision with identification of critical milestones and timelines
- Development of systems tools to support the QI process
- Development and testing of specific changes to the system using the Model for Improvement and PDSA cycles
- Establishment of logs and data collection forms to monitor progress
- Rapid feedback of clinic data to enable the clinic QI team to identify ongoing challenges and develop solutions
- The introduction of PrEP and TasP into services will build on QI strengthened service delivery.
- Staff will be provided with detailed information on what is known about PrEP and TasP and strategies for providing individualized user support.

With support from the experienced QI advisor, the clinic QI team will:

- Set clear goals for service delivery improvement
- Map out the critical steps required for provision of PrEP and TasP to clients
- Develop system tools to support PrEP and TasP provision including data collection tools to monitor progress
- Oversee implementation of PrEP and TasP delivery plan
- Review data and feedback to family planning staff to develop solutions to challenges

This two-step approach of initially strengthening the services and introducing PrEP and TasP using a QI framework will create a cadre of service providers who can remain vigilant about the quality of services provided and cope with unexpected or unanticipated situations, in contrast to a more traditional prescriptive, top-down approach of service delivery.

### 11.3 Supply, storage and dispensing of PrEP drugs

Throughout the study duration, PrEP medication will be supplied free to participants on the project. It is anticipated that Gilead will supply all the medications for the study free. All study drugs will be produced under Good Manufacturing Practices (GMP) conditions. The study drugs will be acquired from Gilead through the procurement team of NACA and distributed to all the study sites. The Study Pharmacist will maintain full accountability records in accordance with Good Clinical Practice (GCP) and legal requirements. These will include pharmacy specific participant logs as well as stock accountability records.

Study product will be securely stored at controlled room temperature below 30°C until required for administration. PrEP should be stored away from direct sunlight.

PrEP will be dispensed directly by designated individuals to enrolled study participants as per Standard Operating Procedures (SOPs) in quantities expected to be sufficient until the participant's next follow-up visit. If a participant needs additional supplies between visits, (s)he will be instructed to contact the study clinic to request additional supplies. Study

participants will be asked to return to the clinic with tablet bottles at each visit. All returned drugs will be reconciled with the number dispensed to the participant and the outcome logged. Further details of the dispensing procedures will be outlined in the Study Specific Pharmacy Procedures Manual. In addition, the recordings from the MEMS Cap will be analyzed and used to corroborate the self-reported adherence and pill counts.

#### 11.4 Recruitment, screening and enrollment

Eligible participants will be enrolled over approximately 12 months. At regular intervals, the Principal Investigators, in consultation with the study team, will assess progress in accrual and retention at each of the sites and may reallocate enrollment numbers and targets across the sites, as deemed necessary to achieve the goals of this trial efficiently. All potential participants will be screened, enrolled and escorted to the respective family planning services, for completion of enrollment visit procedures.

At screening, demographic and behavioral information will be collected, along with laboratory results to establish the risk score and participant eligibility (for HIV-1 uninfected partners – serum creatinine, hepatitis B surface antigen; for HIV-1 infected partners – CD4 count, plasma HIV-1 viral load; for both partners – HIV-1 rapid testing according to national algorithms).

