## 2.0 Study Method

This is a demonstration project to evaluate the effectiveness of three models for the delivery of PrEP and TasP as part of a combination prevention strategy for serodiscordant couples in three states in Nigeria. The overall goal is to identify the best model to facilitate uptake of PrEP as part of a comprehensive HIV prevention package for the HIV negative partner in serodiscordant relationships whose HIV positive partner has not begun ART or

---

has been on ART for less than six months. PrEP (daily oral FTC / TDF) will be offered to the HIV-1 uninfected partner. Uptake of PrEP and TasP and adherence to PrEP will be measured. Factors (individual, facility and community level) that facilitate PrEP and TasP uptake and adherence to PrEP will also be assessed.

HIV-1 infected participants will be offered the opportunity to use ART support services regardless of their CD4 count. This is in line with the current national guidelines on HIV treatment for adults and adolescents (2010:13). The current guidelines enable HIV positive individuals in discordant relationships to have access to ART irrespective of the CD4 count. This project will therefore serve as a measure of the effectiveness of this program in Nigeria.

For each couple, if the HIV-1 infected partner initiates ART, we will discontinue PrEP for the HIV-1 uninfected partner six months later (once viral suppression is typically achieved). If the HIV-1 infected partner declines to initiate ART, or initiates and discontinues, we will continue PrEP. Mixed-methods work will be conducted to understand user preferences, couples decision-making, and barriers to uptake of and adherence to both PrEP and ART.

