In Cross River State, PrEP will be provided through the outpatients department. The model will evaluate the effectiveness of integration of PrEP service delivery using an integrated approach for access and uptake of both PrEP and TasP services for both HIV negative and the index partners.

In Plateau State, PrEP and TasP will be provided through a decentralized service delivery model. PrEP related service will be obtained from a secondary health facility for the first three months as this is considered a critical period in any care program. Thereafter, services would be decentralized to primary and private project satellite clinics (primary and private centres). The satellite centres will provide the three monthly HCT services and monthly drug refill services. Six monthly laboratory assessment of health profiles would however, be conducted at the central hospital.

In Anambra State however, all PrEP and TasP services will be provided through HIV treatment centres with services remaining centralized.

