### 3.0 Objectives

#### 3.1 Primary objectives

- 3.1.1 Optimize, implement and evaluate the effectiveness of an implementation model which integrates PrEP and TasP provision into existing service provision centres.
- 3.1.2 Estimate the cost and cost effectiveness of the PrEP and TasP demonstration project.
- 3.1.3 Model the resources needed to provide scaled up PrEP and TasP access for serodiscordant couples in Nigeria.

**Objective 3.1.1: To optimize, implement and evaluate the effectiveness of an implementation model which integrates PrEP and TasP provision into existing service provision centres.**

The demonstration project will be evaluating the effectiveness of a model of HIV service delivery to couples that promotes and ensures effective PrEP access. Such a model should be able to ensure effective community engagement in ways that improve and support a couple's access and uptake of HIV prevention and treatment interventions, ensure access in hard to reach areas where there are few health facilities, and support sustained quality and consistency of PrEP and TasP services irrespective of place of delivery. The model for delivery of ART based HIV intervention programs for couples for this demonstration project would be designed based on feedback received during the formative research conducted to support this research. The study outcome should help critical stakeholders know how well the study model was able to achieve the desired PrEP service delivery into family planning services. This will help inform decision making on how to institutionalize the program, strategies that are economical and efficient, and how best to make modifications to the program implementation model to increase effectiveness.

The primary outcome of this objective is the measure of the impact that project intervention had on serodiscordant couples' access, uptake and retention in the antiretroviral-based HIV-1 prevention program. Formative and summative evaluations would be conducted. Formative evaluation will be conducted at months 6, 12 and 18 with derived information use to modify the program so as to increase its efficiency. The summative evaluation will be conducted at the end of the project and would help to decide on the effectiveness of the program.

*The primary measure of this objective will be the number of new infections averted by the use of PrEP and TasP.*

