## 4.0 Population

A sample with a size of 600 heterosexual HIV-1 serodiscordant couples will be recruited from ART sites with family planning clinics in three States in Nigeria. Couples who had not

---

56. van de Vijver DA, Boucher CA. The risk of HIV drug resistance following implementation of pre-exposure prophylaxis. *Curr Opin Infect Dis.* 2013;23(6):621-627

had prior access to PrEP and couples whom the HIV positive index partner has not been sero-suppressed despite having commenced the use of ARV will be recruited for the study.

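### Three statements place enrolment, quality-improvement feedback and the question behind objective 3.1.1 in family planning services, which none of the three delivery models in section 2.0 uses

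*Protocol*

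**What the plan says.** Section 2.0 states that the project will "evaluate the effectiveness of three models for the delivery of PrEP and TasP", and separates the models by where services are given. For the first, "In Cross River State, PrEP will be provided through the outpatients department". In Plateau, PrEP services start at a secondary facility for three months, after which "services would be decentralized to primary and private project satellite clinics". In Anambra, services stay centralised in HIV treatment centres. Section 5.0 argues for outpatient and HIV-care integration, and 11.2 describes the outlet to be strengthened as an outpatient or HIV clinic.

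Family planning appears as a setting in three other places:

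- Section 11.4, on enrolment: "All potential participants will be screened, enrolled and escorted to the respective family planning services, for completion of enrollment visit procedures".
- Section 11.2, in the list of tasks for the clinic quality-improvement team: "Review data and feedback to family planning staff to develop solutions to challenges".
- Section 3.1, in the text explaining objective 3.1.1: the study should show "how well the study model was able to achieve the desired PrEP service delivery into family planning services".

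The formal wording of objective 3.1.1 speaks only of a model that "integrates PrEP and TasP provision into existing service provision centres".

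**The concern.** The service setting is what makes the three models different. An instruction that sends every couple at every site to another kind of clinic for part of the process cuts across that difference. Section 11.4 is an operating instruction, and site procedures would be written from it.

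The step it moves matters for the evaluation. Under 11.5, the enrolment visit is where couples are counselled on ART and PrEP, the uninfected partner is offered PrEP and the infected partner is offered TasP or ART. Section 13.1 names uptake as the outcome variable for objective 3.1.1. If that offer is made in a family planning clinic everywhere, first acceptance reflects that clinic and its staff rather than the outlet under evaluation.

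The 11.2 bullet would send improvement data to staff to whom 2.0 gives no part in PrEP delivery. The sentence in 3.1.1 tells readers that the study answers a question about a service it does not test.

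**Working it through.** No arithmetic applies, because the point depends on no rate, effect size or sample-size formula. The check sets side by side the statements that name a setting.

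**Statements that define the delivery setting**

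| Place in the protocol | Setting | Family planning named as the outlet? |
|---|---|---|
| 2.0, Cross River | Outpatient department | No |
| 2.0, Plateau | Secondary facility, then primary and private satellites | No |
| 2.0, Anambra | HIV treatment centres, centralised | No |
| 3.1.1, formal objective | Existing service centres, type not given | No |
| 5.0 | Outpatient care and HIV treatment services | No |
| 11.2, description of the outlet | Outpatient or HIV clinic | No |

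Family planning is the setting in 0 of the 3 models.

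**Statements that place something in family planning**

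| Place in the protocol | What is placed there |
|---|---|
| 3.1.1, explanatory sentence | The delivery question the study should answer |
| 11.2, team task list | Feedback of quality-improvement data |
| 11.4 | Completion of enrolment visit procedures, all participants |

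No other statement reconciles the two groups. Section 11.2 contains both: its outlet is an outpatient or HIV clinic, but its feedback goes to family planning staff.

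**From the instruction to the outcome**

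1. Section 11.4 applies to all participants, and section 8.0 plans 600 couples. The instruction therefore covers all 600 couples at all 3 sites.
2. Section 11.5 puts the first offer of PrEP and TasP at enrolment.
3. Section 13.1 makes uptake the outcome variable for 3.1.1.
4. So the first decision that counts towards uptake would be taken in a setting shared by the sites. Whatever the assigned outlet contributes to that decision drops out of the comparison.
5. What stays specific to each model is what comes later. Section 11.3 gives dispensing to designated individuals under standard procedures and names no family planning clinic. In Plateau, 2.0 places refills and three-monthly testing at the satellites and six-monthly laboratory work at the central hospital.

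Steps 4 and 5 point to dilution of the contrast on initial uptake. They do not point to its loss, or to a bias in favour of one model. The protocol states no expected difference in uptake between models, so the dilution cannot be sized.

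**The case against.** The strongest reply is that the design sections agree with one another and that these are three stray phrases. Sections 2.0 and 5.0, the formal objective and the outlet description in 11.2 are consistent, and a sensible site team would follow them. Section 11.4 moves only enrolment procedures, while follow-up of up to 18 months stays with the assigned outlets. A step common to all sites favours no model. Section 11.2 also provides for clinic data to go back quickly to the clinic's own improvement team, so the outlet staff are not cut off. A family planning unit may also stand in the same hospital as the assigned outlet; the protocol does not say.

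Much of this stands, and it limits the point. It does not remove the contradiction: 11.4 is explicit, covers everyone and governs the visit at which the offer is made. A common step need not be biased to make a difference in uptake harder to see.

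A reader might also infer four stronger things that the protocol does not support:

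- **The trial evaluates or delivers a different intervention.** The formal objective and the three models do not say so, and dispensing and follow-up are not placed in family planning.
- **The outcome of 3.1.1 is defined as family planning delivery.** The same section defines the primary outcome as the effect on couples' access, uptake and retention, with infections averted as the measure. The sentence quoted only says what stakeholders should learn.
- **Section 4.0 is part of the conflict.** Couples "recruited from ART sites with family planning clinics in three States in Nigeria" is a description of the recruiting sites. It fits a plan that includes contraceptive counselling and places no delivery in those clinics.
- **Nearly all PrEP candidates would be men, poorly served by family planning.** Section 1.3 reports, for one programme, that women were 11 times more likely to be the positive partner, which would give 11/(11+1), about 92%, male negative partners. Nothing shows that this ratio applies to couples recruited here, and the protocol does not say how well family planning clinics serve men. Section 10.0 requires both partners to attend the enrolment visit together.

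**Conclusion.** The concern holds as an internal contradiction about service setting. One sentence in 3.1.1, one bullet in 11.2 and one sentence in 11.4 conflict with the models in 2.0 and the outlets named in 5.0 and 11.2. The sentence in 11.4 carries the weight, because it would put the first offer of PrEP and TasP to all 600 couples outside the assigned model and so weaken the comparison on uptake. The other two misdirect feedback and misdescribe the question, without altering an endpoint or an analysis.

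This rests on two assumptions: that 11.4 would be followed as written, and that the setting of the first offer influences acceptance. The second is implicit in a study that compares settings, but the protocol gives no figure for it. If sites in practice complete enrolment at the assigned outlet, only the wording is wrong. The correction should be made before site procedures are finalised.

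**What to change.** - **Section 11.4:** state that enrolment visit procedures are completed at the service outlet assigned to each site in 2.0, and name that outlet for each of the three sites.
- **Section 11.2:** direct quality-improvement feedback to the staff of that outlet.
- **Section 3.1, text under objective 3.1.1:** replace the reference to family planning with delivery through outpatient, decentralised or HIV-clinic services.

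Family planning counselling and contraception can remain service elements, and the site description in 4.0 can stay. The cost is a wording amendment and matching site procedures. Sample size, data collection and analysis do not change.
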